# He Korowai Manaaki (Pregnancy Wraparound Care): Protocol for a Cluster Randomized Clinical Trial

**DOI:** 10.2196/18154

**Published:** 2021-01-29

**Keywords:** maternity, inequity, Indigenous health, Māori, pregnancy, Kaupapa Māori, socioeconomic, primary health care, methodology

## Abstract

**Background:**

Maternal and infant health inequities between Māori (the Indigenous peoples of Aotearoa New Zealand) and New Zealand European women are well documented and cannot be explained solely by socioeconomic status. A research center-iwi (tribal group) partnership aims to address these disparities and improve maternal and infant health outcomes by implementing an augmented maternity care pathway (He Korowai Manaaki) to improve access to services and evidence-informed care.

**Objective:**

The objective of this study is to test whether an augmented maternity care pathway improves Māori infant health outcomes.

**Methods:**

This is a Kaupapa Māori (by, with, and for Māori) cluster randomized clinical trial involving 8 primary care practices allocated to either an intervention arm or control arm. The intervention arm comprises an augmented maternity care pathway (He Korowai Manaaki) offering clinical care through additional paid health care appointments and improved access to social support (eg, housing, transport). The control arm is usual care. The primary outcome is increased timely vaccination for Māori infants, defined as all age-appropriate vaccinations completed by 6 months of age.

**Results:**

Recruitment commenced in November 2018 and was completed in June 2020, with 251 enrolled women recruited in intervention primary care practices before 20 weeks of pregnancy. Publication of results is anticipated in late 2023.

**Conclusions:**

The results will inform primary health care policy including whether the provision of augmented maternal care pathways reduces disparities in the structural determinants of health. If effective, He Korowai Manaaki will strengthen the health and well-being of pregnant Māori women and their babies and improve their health outcomes, laying a strong foundation for lifelong health and well-being.

**Trial Registration:**

Australian New Zealand Clinical Trials Registry ACTRN12619001155189; https://tinyurl.com/yypbef8q

**International Registered Report Identifier (IRRID):**

DERR1-10.2196/18154

## Introduction

### Background

Protecting the health and well-being of expectant mothers and their families helps ensure that they and their baby/ies are well cared for and supported to have good maternal outcomes. In Aotearoa New Zealand, Indigenous Māori women have higher rates of adverse pregnancy outcomes compared to non-Māori women. Māori infants have an infant death rate of 5.9 per 1000 births compared to 3.2 per 1000 births among non-Māori [1]. Māori pregnant women and children also experience substantial socioeconomic disadvantages. Even so, the health inequities between Māori and New Zealand European women and infants are well documented and cannot be explained solely by socioeconomic status [2]. Reducing these health and socioeconomic disparities is an urgent priority.

At the invitation of the iwi (tribal group), He Korowai Manaaki (a protective cloak) was designed to surround pregnant woman and their children with the best evidence-informed, timely care and the best environment. As an augmented maternal care pathway, He Korowai Manaaki was designed to improve health and well-being through pregnancy and baby’s first 2 years of life and beyond.

Aotearoa New Zealand’s unique midwifery-led model of maternity care, established nearly 30 years ago, was purported to hold the potential to improve health outcomes for Māori [3]; however, Māori women and whānau (family) continue to experience persistent health inequities that impact well-being throughout the maternity continuum [4]. Underrepresentation of Māori midwives at all levels of the profession is indicative of a colonized infrastructure with Māori childbirth knowledge treated with skepticism [4].

Most women begin their pregnancy journey with their primary health care provider; however, the current model does not easily support continued primary health care practice involvement during pregnancy nor postpartum. Transitioning to a lead maternity carer (LMC; typically a midwife) can lead to fragmented, siloed care, inhibiting a seamless pregnancy pathway [2] and potentially contributing to health disparities for Māori women and babies [5].

Therefore, changes in the structure of the maternity health system are required, as improved coordination between midwives and general practitioners could be of great benefit for both equity of outcomes and efficiency of health service delivery [6].

### Iwi Partnership

The research center Te Tātai Hauora O Hine (The Centre for Women’s Health Research, Victoria University of Wellington) was invited to partner with iwi/tribal group Ngāti Pāhauwera and develop a wraparound approach to maternity care. The aim of this approach was the provision of a seamless maternal and infant care pathway with improved access to both clinical and social support [7].

The guiding principles of the Ngāti Pāhauwera strategic plan are *Pakatō i te ata, Pakatō i te ahiahi, Māuri mahi Māuri ora* (planning for the future health and well-being of the people), and *Mahia nga māhi o Kahukura* (imagining and creating a better future). These guiding principles provide foundations for the research partnership [7] and the resulting He Korowai Manaaki pathway (ACTRN12619001155189).

Grounded in a Kaupapa Māori (by, with, and for Māori) inquiry paradigm, this research prioritizes Māori ways of knowing and being, promotes a structural analysis of inequality [8], and aims to benefit Māori through the reduction of disparities [8-10]. The research practices reflect tikanga Māori (Māori customs), including the importance of place, relationships, and Māori self-determination [8,9].

### Aims

This study aims to implement an augmented maternity care pathway (He Korowai Manaaki) to improve Māori maternal and child health outcomes and to improve access to services (health, education, Well Child Tamariki Ora [WCTO], oral health, contraception, general practice) for pregnant Māori women and their infants.

We hypothesize that the He Korowai Manaaki pathway, with early, evidence-informed care and ongoing wraparound support opportunities, will improve the health outcomes of Māori infants. If successful, this pathway will serve as a prototype for an augmented national maternity care pathway.

## Methods

### Design

This study is a cluster randomized clinical trial with 2 study arms for pregnant women enrolled with primary care practices (PCPs). Practices are the unit of randomization. Intervention PCPs utilize the He Korowai Manaaki pathway for the pregnant women in their practice. Control PCPs continue usual care. For collection of data, all women in the intervention are individually consented, in contrast to the control arm where deidentified data is collected without individual consent.

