### Study Sites

All 15 PCPs in the urban Hawkes Bay region of Aotearoa New Zealand were approached; 8 provided informed written consent to participate in the cluster randomized clinical trial and were randomized: 4 to intervention and 4 to control. All pregnant women enrolled as a patient of an intervention PCP are eligible for the intervention.

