### Intervention Arm (He Korowai Manaaki)

The He Korowai Manaaki intervention addresses both clinical care (pregnancy, postpartum, neonatal, and reproductive health) and the structural determinants of health (eg, housing, transport) with a best-practice pathway. He Korowai Manaaki includes responses to recommendations from the New Zealand Perinatal and Maternal Mortality Committee [14] and is in line with recommendations to address structural determinants of health by the Select Health Committee Inquiry into Improving Child Health Outcomes [15]. As a practice service change, He Korowai Manaaki is facilitated through primary care–held appointments including an extended first visit (First Touch), a follow-up visit, a third trimester visit, and a 6-week postnatal whānau (family) visit. Usual lead maternity care continues throughout.

General practitioners, nurse practitioners, and practice nurses at intervention PCPs were asked to attend an introductory training session on He Korowai Manaaki to enable the practice service change. The in-practice session provided by the researchers included education refreshers of evidence-based antenatal care, postnatal care, and contraception as well as information on the 4 study-funded appointments and utilization of the pregnancy wraparound care computerized advanced form installed into their practice management system. Education refresher sessions are provided by the researchers and associated experts over the course of the trial.

Clinicians in intervention PCPs work from the computerized advanced form to support care, screening, and navigation to allied services. This includes referrals to specialist care and services meeting the needs of wraparound care (eg, housing program, social work services, driving licensing programs, and dental practices).

Intervention practices are also supported to provide contraception of the woman’s choice, free of charge (see third trimester appointment and 6-week postnatal appointment in Textbox 1) and support with transport to pregnancy-related appointments (see First Touch appointment in Textbox 1).

Posters and published material on display at each intervention practice inform the enrolled population of the He Korowai Manaaki practice change taking place for the duration of the research project. All women identifying as pregnant in a primary care appointment are informed that their practice is offering an augmented pathway of care for pregnant women as part of the research project.

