Information about the project is also shared with individual women by the general practitioner, nurse practitioner, or practice nurse. Each woman is asked to provide informed written consent for their deidentified outcome data (pregnancy and infant health information) to be shared with the research group in the future. The augmented pathway visits (Textbox 1) are explained, with the First Touch appointment then being offered to all women (with no data being shared for nonconsenting women). All women are then invited to attend the other study appointments (free of charge), and a recall for the next appointment is set.

There are no exclusions. The augmented pathway of care is available at any stage of pregnancy, for all pregnancies (low-risk and high-risk).

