### Data Collection

The data for our study are generated from national and local information collections, as described by Filoche et al [16]. In Aotearoa New Zealand, the Ministry of Health (MOH) is responsible for the oversight and funding of the country’s 20 district health boards. Select clinical information is routinely reported by each health board to the MOH and is collated into national datasets with operational responsibility by the Client Insights and Analytics group. Outcome data will be collected using Aotearoa New Zealand’s unique patient National Health Index (NHI) number to source clinical and demographic data from multiple national datasets (Table 1).

At study end, intervention practices will send the NHIs of women who have provided consent for their deidentified outcome data to be collected and analyzed (linked to the NHI of an infant) to the MOH. The MOH will also receive from each control practice the NHIs of women registered with them during the study’s recruitment period. To identify the control group (women enrolled with PCPs, pregnant during the study period) and the associated linked infant(s) following the relevant designated time period (Figure 1), the MOH will match the NHIs provided by the control practices to national datasets containing maternity, pregnancy, and delivery information (eg, the National Maternity Collection and the National Minimum Dataset).

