### Analysis

Data analysis will occur as soon as outcome data are available for the intervention and control arms. Within a Kaupapa Māori inquiry paradigm [8-10], the primary analysis is for Māori, with secondary analysis for non-Māori [17]. An intention-to-treat analysis will be undertaken [18] using individual participant data. All pregnancies will be analyzed (regardless of the number of He Korowai Manaaki appointments attended), with the primary cohort being women seen in a PCP before 20 weeks of pregnancy.

The rate of infant hospitalizations will be analyzed using Poisson regression, and if there is evidence of overdispersion or underdispersion, then negative binomial model will be used. A generalized linear mixed model with a logit link will be used to analyze binary outcomes, and a linear mixed model will be used to analyze continuous outcomes. All regression models will adjust for potential personal and care-related confounders and for the effect of clustering within practices. Sensitivity analyses will be undertaken for the primary outcome to determine the impact of missing data, and per protocol analyses will be conducted. The consistency of effects for prespecified subgroups will be assessed using tests for heterogeneity.

Descriptions of rates, rate ratios, odds ratios, and respective 95% confidence intervals will be reported. Results will be aggregated, and no individual practice will be identifiable.

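### Intervention women are analysed only if identified at a practice and individually consented, controls by register matching without consent, so the comparison is not intention-to-treat and is open to selection bias

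*Protocol article*

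**What the plan says.** Practices are randomized (Study Sites: "8 provided informed written consent to participate in the cluster randomized clinical trial and were randomized: 4 to intervention and 4 to control"), and the population they bring is broad: "All pregnant women enrolled as a patient of an intervention PCP are eligible for the intervention".

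The routes into the data then differ.

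- **Intervention arm.** Women are reached at the practice: "All women identifying as pregnant in a primary care appointment are informed that their practice is offering an augmented pathway of care" (Intervention Arm). Clinicians there ask for written consent to data sharing, "with no data being shared for nonconsenting women". At study end, "intervention practices will send the NHIs of women who have provided consent for their deidentified outcome data to be collected and analyzed" (Data Collection).
- **Control arm.** "The MOH will also receive from each control practice the NHIs of women registered with them" for the recruitment period (Data Collection). The MOH then finds the pregnancies by matching to national datasets. Neither consent nor a practice visit is a condition of being identified.

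The Design section states the contrast outright: "all women in the intervention are individually consented, in contrast to the control arm where deidentified data is collected without individual consent".

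Under Analysis, "An intention-to-treat analysis will be undertaken", with women who had practice contact before 20 weeks as the primary cohort. Limitations appeals to intention-to-treat as the accepted standard and does not mention the difference in ascertainment.

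**The concern.** Randomizing practices makes the arms comparable, within the limits of 8 clusters, for all pregnant women enrolled at those practices. It does not make comparable two groups picked out afterwards by different rules. One group is filtered by attendance and by willingness to sign when asked by staff who know the allocation. The other is drawn from a register.

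The primary outcome is timely infant vaccination, which itself reflects engagement with health services. Attending and consenting plausibly mark the same trait. If the least engaged families drop out of one arm only, a difference can appear with no effect of the pathway. Including every consenter regardless of appointments attended does not bring back eligible women who were never captured. The article intends the result to inform a national maternity pathway, so this bears on the trial's main conclusion.

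**Working it through.** **1. The plan's own figure.** Sample Size gives 65% v 83.5%, two-sided α 0.05, 80% power, cluster size 27 and ICC 0.01. Design effect = 1 + (27 − 1) × 0.01 = 1.26. Per group:

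| Formula | Before clustering | × 1.26 |
|---|---|---|
| Pooled variance | 87 | 109.6 |
| Unpooled variance | 83.8 | 105.5 |
| Arcsine | 85.1 | 107.2 |

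The stated 108 reproduces, with power of 79.6% at 108 per group. The sample size is not in dispute; it supplies the standard error below.

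**2. The entry rules side by side.**

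| Step | Intervention | Control |
|---|---|---|
| Eligible | All enrolled pregnant women | All enrolled women pregnant in the period |
| Found by | Practice appointment | MOH matching of the register |
| Consent for data | Individual, written | None |
| Decliners | No data | Not applicable |
| Contact before 20 weeks | Known: 251 of 293 enrolled (Results) | No listed source described as recording it |

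Results gives no number of eligible women for the intervention practices, so the captured share cannot be worked out.

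**3. Size of the possible bias (illustration).** Let c be the share of eligible intervention women captured, and g the vaccination gap between captured and uncaptured women. Neither is in the article; both are assumed. With no true effect and 65% vaccinated in both full populations, the captured rate pc satisfies

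0.65 = c × pc + (1 − c) × (pc − g), so pc − 0.65 = (1 − c) × g.

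The null standard error is √(2 × 0.65 × 0.35 × 1.26 / 108) = 0.073. Two-sided type I error = P(|Z + bias/SE| > 1.96).

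| Missed (1 − c) | Gap g | Bias | Bias/SE | Type I error |
|---|---|---|---|---|
| 10% | 10 points | 1.0 point | 0.14 | 5.2% |
| 30% | 15 points | 4.5 points | 0.62 | 9.5% |
| 40% | 20 points | 8.0 points | 1.10 | 19.5% |

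Against the 18.5-point target, 8 points is 8/18.5 = 43%. With g negative, the same formula gives a bias against the pathway.

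**4. Power of a cluster-level comparison under one rule.** With 4 v 4 practices (6 degrees of freedom), 108 per arm and the full 18.5 points, SE = √[(0.65 × 0.35 + 0.835 × 0.165) × 1.26 / 108] = 0.065. The ratio is 2.83, and noncentral t power is about 66%. If 70% were captured and the pathway did nothing for the rest, n = 108/0.7 = 154 per arm and the effect is 0.7 × 18.5 = 13 points. Cluster size is 38.5, the design effect 1.375, SE 0.060, and power about 45%.

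**The case against.** **The before-20-weeks cohort.** A reader might infer that the control arm counts every registered pregnant woman, including those who never visited. The article does not go that far for the primary cohort. The rule under Analysis is not confined to one arm, and read literally it excludes a control woman with no early practice contact. That would shrink the attendance part of the problem. But Data Collection defines controls only as enrolled and pregnant, and no source in Table 1 is described as recording such a visit. Table 1 lists examples and local collections are also mentioned, so a source may exist. The Control Arm section only presumes that most controls had early contact. Even if the rule were applied in both arms, the consent filter would remain on one side.

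**Direction.** A reader might infer that the bias is shown to favour the pathway. It is not. Free visits, transport help and housing support could draw higher-need women, which would push the other way.

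**Adjustment.** All models adjust for personal and care-related confounders. These are unnamed, and willingness to consent is not observed in controls, so adjustment cannot be relied on to remove this selection.

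**Infant linkage.** A reader might also infer that infants are linked differently in the two arms. The parenthesis in Data Collection does not say who links or how, so nothing is built on it here.

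**A SAP may deal with it.** A SAP could relabel the analysis or add sensitivity analyses. It cannot recover women whose identifiers are never sent.

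**Conclusion.** The point stands on the article's own text. The arms are ascertained by different rules after allocation, and leaving out eligible intervention women who were not identified or did not consent contradicts the intention-to-treat claim under Analysis and Limitations. Neither randomization of practices nor the planned adjustment removes the resulting selection.

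A bias in favour of the pathway is the likely direction, by inference from the nature of the outcome. Its size is unknown. The range of 1 to 8 points rests wholly on assumed capture (60–90%) and gap (10–20 points), on a crude comparison, and on the whole loss falling in one arm. At the low end it is negligible. If the 20-week rule were truly applied to controls, the relevant share missed would be smaller.

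**What to change.** **(a) Preferred, subject to ethics and iwi agreement.** The MOH identifies mother–infant pairs in all 8 practices by one rule: registered with the practice and pregnant in the window. Where decliners' individual data cannot be used, only practice-level counts are returned (Māori infants, and the number fully vaccinated by 6 months). This is reported as the intention-to-treat comparison, with the consenters-only comparison as a labelled secondary analysis.

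No new participants are needed, and data collection was not due to start until early 2022. The approval is not a formality. Women were recruited on the footing that decliners' data would not be shared, and even aggregate counts draw on their outcomes. The effect is also diluted by women the pathway never reached, and power with 4 v 4 clusters is about 66%, or about 45% in the 70% capture scenario. Both figures should be stated.

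**(b) If approval is not given.**

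- Drop the intention-to-treat label and describe the analysis as consenting intervention women against register-identified controls.
- Apply the before-20-weeks rule to both arms, naming the data source for controls, or to neither.
- Report eligible and consented numbers for each intervention practice.
- Add a sensitivity analysis for selection over a stated range of capture rates and gaps, including gaps of the opposite sign.
- List the asymmetry under Limitations.

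Option (b) costs text, a count of eligible women at four practices and a short analysis. The selection itself remains.

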### Research Approval

Research ethics approval was granted by the Health and Disability Ethics Committee of New Zealand (17/STH/136) in August 2017.

### Study Sites

All 15 PCPs in the urban Hawkes Bay region of Aotearoa New Zealand were approached; 8 provided informed written consent to participate in the cluster randomized clinical trial and were randomized: 4 to intervention and 4 to control. All pregnant women enrolled as a patient of an intervention PCP are eligible for the intervention.

### Sample Size

A total of 8 practices and 216 Maori participants (4 practices and 108 Maori participants in each group) will provide 80% power at a two-sided α of .05 to detect an 18.5% difference in the proportion of infants who receive all age-appropriate vaccinations by 6 months of age between the groups. For these figures, we have assumed an average cluster size of 27, intracluster correlation coefficient of 0.01, and that 83.5% of the infants will receive all age-appropriate vaccinations by 6 months of age in the intervention group and 65% in the control group. Our total sample size requires 432 pregnancies (216 control, 216 intervention).

Based on the expected recruitment rate and pregnant women meeting the entry criteria for the core intervention (ie, seen in a PCP before 20 weeks of pregnancy), He Korowai Manaaki is offered through intervention practices to all pregnant women for approximately 18 months from the commencement of the study to obtain the required sample size.

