### Randomization

Practices are the unit of randomization. Each of the 8 PCPs was randomly allocated to either the intervention arm (He Korowai Manaaki) or the control arm (usual care) of the trial. Covariate constrained randomization [11,12] was used to minimize potential imbalance between intervention and control arms in the size of the Māori population aged less than 1 year. Information on enrollment size and numbers of Māori patients aged less than 1 year was collected for each of the 8 participating PCPs. All possible allocations of these PCPs to the 2 trial arms were then enumerated using an algorithm blinded to the practice names. The list of allocations was then narrowed down to the ones that gave approximate balance in the numbers of Māori aged less than 1 year across the 2 arms, with each arm having 4 clusters (PCPs). Finally, the actual allocation was chosen randomly from this constrained list, thereby achieving an acceptable allocation while retaining randomness in the selection process. No practices dropped out of the study.

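### The stated 80% power rests on a many-clusters normal approximation; with 8 practices, a test on 6 degrees of freedom has about 64–66% power on the same inputs

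*Protocol article*

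**What the plan says.** The Sample Size section of the protocol article gives a complete set of inputs. It claims that the planned sample "will provide 80% power at a two-sided α of .05 to detect an 18.5% difference" on the primary outcome, timely infant vaccination. Each arm has 4 practices and 108 Māori participants. For the clustering, the authors write that "we have assumed an average cluster size of 27, intracluster correlation coefficient of 0.01". The vaccination proportions behind the calculation are 0.835 under the intervention and 0.65 under usual care. No formula, reference distribution or degrees of freedom is named.

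The Study Sites and Randomization sections confirm that whole practices were randomized, 4 to each arm. The Analysis section plans a generalized linear mixed model with a logit link for binary outcomes, fitted to individual data and adjusted for clustering within practices. It names no adjustment for the small number of practices.

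**The concern.** The comparison between arms rests on 8 randomized units. Inflating an individually randomized sample size by a design effect and then using 1.96 treats the between-practice variance as known. Here it has to be estimated from 8 practices, which leaves 8 − 2 = 6 degrees of freedom.

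A power of 80% and a two-sided α of .05 are stated together. If the 80% needs a test whose error rate exceeds .05 when the ICC is not known, the two do not belong in one sentence. A null result read against 80% power would then look more informative than it is, and a positive result from an uncorrected test would look stronger than it is.

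**Working it through.** **Inputs (all from the Sample Size section):** p₁ = 0.835, p₂ = 0.65, difference 0.185; 4 practices × 27 = 108 per arm; ICC 0.01; two-sided α .05.

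**Step 1. Reproduce the plan's figure.**
- Design effect = 1 + (27 − 1) × 0.01 = 1.26. Effective number per arm = 108 / 1.26 = 85.7.
- SE (unpooled) = √[(0.835 × 0.165 + 0.65 × 0.35) × 1.26 / 108] = √[(0.1378 + 0.2275) × 1.26 / 108] = 0.0653.
- Difference / SE = 0.185 / 0.0653 = 2.834.
- Normal power = Φ(2.834 − 1.960) = 80.9%. The version with pooled variance under the null gives 79.6%.

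Both match the stated 80%. Other candidates do not: 74.2% with a continuity correction, and 88.0% (pooled) without the design effect. The article does not name its formula, so the normal approximation is inferred, but the match is close.

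**Step 2. Same inputs, t on 6 degrees of freedom.**
- Critical value 2.447.
- Noncentral t with noncentrality 2.834 (unpooled): power **65.9%**. With noncentrality 2.770 (pooled): **63.9%**.
- Simulated t-test on practice proportions (beta-binomial data, 4 × 27 per arm, 200,000 runs): power 65.7%, type I error 5.1%.
- With ICC set to 0, unpooled power on 6 df is still only 75.5%, so no non-negative ICC brings this test to 80%.
- Difference detectable with 80% power at ICC 0.01: 65% versus 86.4%, or 21.4 points (unpooled variance).

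**Step 3. The planned logit mixed model at ICC 0.01 (simulated, equal practices of 27).**

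| Cutoff for the Wald statistic | Type I error | Power |
|---|---|---|
| 1.96 (uncorrected) | 6.0–6.8% | 81–82% |
| about 2.03 (calibrated to 5% at ICC 0.01) | 5% | about 79% |
| 2.447 (6 df) | 1.9–2.4% | 66% |

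**Step 4. Other ICC values. These are assumptions; the article gives only 0.01.**

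| ICC | Power, t on 6 df (unpooled) | Type I error, uncorrected Wald z in the mixed model |
|---|---|---|
| 0.01 | 66% | 6–7% |
| 0.03 | 52% | 9.4–9.7% |
| 0.05 | 42% | 11.4% |

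**The case against.** The strongest reply is that 66% belongs to a test the protocol does not plan. The Analysis section calls for a mixed model on individual data, and such a model also uses within-practice information. At an ICC of exactly 0.01, a cutoff calibrated to a true 5% level gives about 79% power, and the 6-df cutoff makes the model conservative, with type I error near 2%. That is correct. A reader might infer from the 6-df result that 80% power is unattainable at a true 5% level. The plan's own inputs and model do not support so strong a reading.

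The calibrated cutoff, however, is available only if the ICC is known to be 0.01. At assumed values of 0.03 and 0.05 the uncorrected test runs at about 10% and 11%. Without that knowledge the test needs protection of the 6-df kind, and then the 80% is not delivered.

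A second reply is that the small-sample method is commonly left to the statistical analysis plan, which is not shown. So its absence from the article is not itself an error. But if that plan does specify a 6-df correction, the article's 80% still does not describe the resulting test.

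A third reply is that the sum is right for the formula used. It is: the issue is the choice of approximation, not a slip in arithmetic.

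A reader might also want to add unequal practice sizes, infants without outcome data, or the Māori share of the 251 women in the primary cohort. The article gives no figures for the first two. The third is a separate recruitment question. None of them is needed for this point.

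**Conclusion.** The point holds in a bounded form. The 80% follows from a normal approximation suited to many clusters. On identical inputs, a test that protects α without knowing the ICC has 64–66% power, about 14 to 16 points lower, so its type II error is about 34–36% rather than 20%.

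The planned model with an uncorrected Wald z test reaches about 80%, at a type I error of about 6–7% if the ICC is 0.01 and more if it is larger.

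These figures assume equal practices of 27, 108 Māori infants per arm with outcomes, and a between-practice comparison on 6 df. The mixed-model error rates come from simulation.

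**What to change.** 1. **Restate the power** in the Sample Size section, or in the analysis plan and results report if the published article cannot be changed: *With 8 practices and 108 Māori infants per arm, 65% versus 83.5% and ICC 0.01, power is about 66% for a small-sample test on 6 degrees of freedom, which has 80% power for a difference of about 21 points. Power of 80% for 18.5 points holds only under a large-cluster normal approximation.*
2. **Correct the primary comparison.** Apply a small-number-of-clusters correction to the mixed model in the Analysis section: either 6 df, or a permutation test over the constrained list of allocations. Check the length of that list before choosing the second. There are 70 ways to split 8 practices 4 and 4. If each allocation's mirror image is also on the list, the smallest two-sided p-value is 2 / (list length), so at least 40 allocations are needed to reach .05. If the analysis plan already contains such a correction, only item 1 remains.
3. **Show sensitivity to the ICC**, labelled as assumed values: about 52% at 0.03 and 42% at 0.05.

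Cost: the stated power is less favourable. With 6 df the interval multiplier rises from 1.96 to 2.447, so intervals on the model scale are about 25% wider (2.447 / 1.96 = 1.25), and the test is conservative if the ICC really is 0.01. No further participants or data are needed, and according to the Results section outcome data collection had not begun when the article was written.
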